### Study Design

The EZI-PrEP study will be a 2×2 factorial, 4-arm, open-label, multi-center, randomized, controlled, noninferiority trial. Study participants will be randomized to 1 of 4 arms: (1) in-clinic monitoring every 3 months (standard of care), (2) in-clinic monitoring every 6 months, (3) online monitoring every 3 months, or (4) online monitoring every 6 months (Figure 1). The study will be implemented at SHCs in Amsterdam, Rotterdam-Rijnmond, Haaglanden, and Gelderland-Zuid (Figure 2). For each individual participant, the planned observation time is 24 months, starting after eligibility screening and enrollment.

All study participants will receive access to a smartphone app (the “EZI-PrEP app”), which contains a diary. Participants will be required to complete this diary daily during the first 18 months of the study period. This information will be used to measure the primary outcome (ie, unprotected acts). DBSs will be collected at months 6 and 12. Routine clinical data registered during PrEP monitoring visits and any additional STI testing or treatment visits from inclusion until the final monitoring visit at month 24 will be retrieved from the national STI surveillance system. Participants will be requested to complete 5 questionnaires (at baseline and at 6, 12, 18, and 24 months) to collect data on PrEP intake; sexual behavior; psychosocial characteristics; and the experiences, acceptability, and usability of the interventions. We will extract automatically registered data on app usage from the app.

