To determine whether the incidence rates change over time, we will model the number of unprotected acts as a function of 1-month intervals using Poisson regression (or negative-binomial regression, if the standard deviation is far greater than the mean of the outcome, ie, overdispersion) and test for changes in time using a Wald χ^2^ test. We will test for the interaction between time and intervention arm.

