### Power and Sample Size Calculation

We assume that the primary outcome measure of unprotected acts will be Poisson distributed with the total number per 100 person-years given as an incident rate (λ) and the total time during monitoring (*t*). We define the incidence rate in the experimental arm as λ_e_ and the incidence rate in the control arm as λ_c_. We aim to reject the null hypothesis that the ratio λ_e_/λ_c_ is greater than or equal to a predetermined noninferiority ratio (r). We consider that a noninferiority ratio of 1.8 is able to preserve clinically acceptable noninferiority bounds with increasing λ.

In a previous PrEP study in the Netherlands (Amsterdam PrEP demonstration project [“AMPrEP study”]), the overall incidence rate of unprotected acts was 78/100 person-years [50]. The AMPrEP study included participants with a high number of sex partners and very high incidence of bacterial STIs. Participants of the NPP have reported fewer casual sex partners and have a lower incidence of bacterial STIs [55]. The EZI-PrEP participants are therefore expected to have fewer unprotected sex acts than the AMPrEP participants. We expect the incidence rate of unprotected acts in the experimental arm (λ_e_) and control arm (λ_c_) to be at least 36/100 person-years. We also assume a median monitoring time of 18 months. Using a Bonferroni-corrected 1-sided type 1 error of 0.0125 (=0.025/2 for a total of 2 comparisons), we will need 368 participants to have 90% power to demonstrate noninferiority using the test statistic based on maximum likelihood estimators from Stucke and Kieser [56]. If λ is higher than 36/100 person-years, we will have sufficient power to demonstrate noninferiority. Considering expected loss to follow-up, we have increased the target sample size by 20%, and thus, the total required sample size is 442.

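### The monthly-count model names no allowance for correlation within participants, so its Wald tests for time and time-by-arm can be too liberal if individual risk varies over time

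*Protocol article*

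**What the plan says.** The last paragraph of Data Analysis, Primary Outcome, in the protocol article sets out a supporting analysis of change over time: "we will model the number of unprotected acts as a function of 1-month intervals using Poisson regression". The stated fallback is "or negative-binomial regression, if the standard deviation is far greater than the mean of the outcome, ie, overdispersion". The plan is then to "test for changes in time using a Wald χ^2^ test", and: "We will test for the interaction between time and intervention arm".

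Under Study Design, the outcome data come from a diary: "Participants will be required to complete this diary daily during the first 18 months of the study period". One-month intervals therefore give up to 18 counts per participant. The sample size section expects the rate of unprotected acts "to be at least 36/100 person-years" and adds: "We also assume a median monitoring time of 18 months".

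The article does not say whether the unit is the person-month or the monthly total per arm. It names no random effect, GEE or clustered variance, and it gives no significance level for these two tests.

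**The concern.** The paragraph does fix a method: model, fallback, trigger for the fallback, and test. The one safeguard addresses extra variance of a count. It does not address correlation between counts from the same person, because standard negative-binomial regression also takes its observations as independent.

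If the correlation takes a harmful form, the standard errors of the time slope and of the time-by-arm term are too small. The interaction test is the planned look at whether a care modality drifts away from its comparator during follow-up. A test that is too liberal could report a drift that is only noise.

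**Working it through.** **Inputs.** From the article: 0.36 events per person-year, which is 0.36/12 = 0.03 per person-month; 18 monthly counts per person. Assumed, because the article gives none: two-sided 5% tests, a linear time term, no true time or arm effect, and the size and form of the heterogeneity. The article states no figure for this model that could be reproduced.

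**Closed form, complete follow-up.** Centre the months at their mean, d = t − 9.5. Then Σd² = (18³ − 18)/12 = 484.5. Let person-level risk have mean 1 and variance v. Let each 6-month episode carry an independent multiplier with mean 1 and variance w. Relative to the naive Poisson variance, the true variance of the slope is

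R = 1 + 0.03 × (1 + v) × w × Σ(episode sums of d)² / Σd².

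The stable part v does not appear by itself, because it multiplies (Σd)² = 0. The episode sums of d are −36, 0 and 36, so the ratio is 2592/484.5 = 5.35. Negative binomial scales the naive variance by K = 1 + 0.03 × [(1 + v)(1 + w) − 1]. The rejection rate is 2 × [1 − Φ(1.96/√R)] for Poisson, with R/K in place of R for negative binomial. With equal arms the same holds for time-by-arm. The number of participants cancels, so a larger trial does not cure the problem.

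- v = 4, w = 0: R = 1, K = 1.12. Poisson 5.0%, negative binomial 3.8%.
- v = 2, w = 1: R = 1 + 0.03 × 3 × 1 × 5.35 = 1.48, K = 1.15. Poisson 10.7%, negative binomial 8.4%.
- v = 4, w = 2: R = 1 + 0.03 × 5 × 2 × 5.35 = 2.60, K = 1.42. Poisson 22.5%, negative binomial 14.8%.

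**Simulation.** Percent rejected, time / time-by-arm. Stable-level, serial and slope rows: 368 people, 1,500 to 4,000 replicates. Episode rows: 442 people, 1,000 replicates.

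| Assumed heterogeneity | Poisson | Negative binomial | Participant-clustered |
|---|---|---|---|
| Stable level, variance 1 | 5.5 / 4.9 | – / 4.7 | 5.6 / 5.2 |
| Stable level, variance 4 | 5.4 / 5.1 | – / 4.1 | 6.5 / 6.3 |
| Stable level, variance 8 | 4.9 / 5.2 | – / 3.0 | – |
| AR(1), correlation 0.8, variance 4 | 9.4 / 9.0 | 8.1 / 7.5 | 6.1 / 5.6 |
| AR(1), correlation 0.8, variance 8 | 13.0 / 12.8 | 9.7 / 9.7 | 5.9 / 6.7 |
| Slopes differ (SD 0.8 per year), variance 4 | 9.7 / 9.1 | 7.6 / 7.1 | 6.8 / 6.1 |
| Slopes differ, variance 8, 20% dropout | 11.1 / 12.0 | 6.7 / 8.5 | 5.9 / 7.5 |
| Level variance 2, 6-month episodes variance 1 | 10.7 / 11.0 | 8.8 / 8.7 | 5.8 / 6.5 |
| Level variance 4, 6-month episodes variance 2 | 21.9 / 20.9 | 14.6 / 14.9 | 6.6 / 7.2 |

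A stable level with 20% random dropout gave 5.1-6.4% for Poisson and 3.4-4.7% for negative binomial. The closed form and the simulation agree within Monte Carlo error, which is at most √(0.22 × 0.78/1000) = 1.3 percentage points.

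**Would a random intercept repair it?** With complete balanced data, a Poisson model with a gamma random intercept factorises into person totals and a multinomial over months. Its slope and model-based standard error then equal the naive Poisson ones. Simulation (442 people, 4,000 replicates) confirms this: 11.1 / 10.6% with variances 2 and 1, and 22.1 / 21.3% with 4 and 2.

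**The case against.** The strongest reply is that the source is a journal article. Naming Poisson regression does not exclude a clustered variance, and such detail is often left to the full protocol or analysis plan. This stands in part: the article never says that a person's months are treated as independent, and a reader who infers that goes beyond the text. What remains is that the paragraph chose to state a variance safeguard, and that safeguard covers only part of the problem.

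A second reply is that repeated counts do not by themselves inflate these tests. That stands fully. A stable person effect cancels from a contrast over time, and negative binomial is then slightly conservative. A reader might infer that the tests give too many false positives in general; the article supports no such claim. Inflation needs risk that changes within a person, or slopes that differ between people. The article makes this plausible, since participants may switch between daily and event-driven use and adherence is studied against mood and stress over time, but it gives no magnitude.

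A reader might also carry the point over to the comparison of arms. Person-level heterogeneity does affect a test of total counts between arms, but this paragraph announces no such test. That comparison is the primary rate ratio and a separate matter.

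**Conclusion.** The point holds conditionally. Under stable differences between participants, both Wald tests stay near the nominal 5%. Under the assumed episodic, serially correlated or slope-varying risk, the false-positive rate is roughly 9-22% for Poisson and 7-15% for negative binomial, against about 5-8% with participant-clustered standard errors. The upper ends rest on the strongest scenario, with level variance 4 and 6-month episodes of variance 2. All of these figures assume a linear time term and two-sided 5% tests.

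The noninferiority conclusions rest on the two crude rate ratios and their confidence limits, and no decision rule uses this model. It is a minor improvement to a supporting analysis.

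**What to change.** State that the unit is the person-month, with log observed diary time as offset. Base the Wald tests for time and time-by-arm on participant-clustered (robust) variance, or on GEE with robust variance. Do not rely on a random intercept with model-based standard errors, which leaves episodic correlation uncorrected.

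The cost is one line of text, with the same data. The robust variance is itself slightly liberal with so few events (442 × 18 × 0.03 ≈ 239 expected with complete diaries), as the 5-8% range shows.

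### The switch to negative-binomial regression compares the standard deviation, not the variance, with the mean, so at monthly intervals its outcome depends mainly on an unstated counting unit

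*Protocol article*

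**What the plan says.** In the protocol article, Data Analysis, Primary Outcome, the last paragraph deals with change in the incidence rate over time: "we will model the number of unprotected acts as a function of 1-month intervals using Poisson regression". Negative-binomial regression replaces Poisson "if the standard deviation is far greater than the mean of the outcome, ie, overdispersion". Change over time is then tested with a Wald chi-square test, and the interaction of time with intervention arm is tested as well. The paragraph does not say whether a count belongs to one participant in one month or to a whole group in one month. It gives no number for how much greater the standard deviation must be.

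The figures needed to try the rule out are in Power and Sample Size Calculation. The article states "We assume that the primary outcome measure of unprotected acts will be Poisson distributed", and expects the rate in both arms "to be at least 36/100 person-years". For the previous Dutch PrEP study it reports that "the overall incidence rate of unprotected acts was 78/100 person-years".

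**The concern.** A Poisson count has variance equal to its mean, so its SD is the square root of the mean and SD/mean is 1 divided by that square root. The ratio is large when the mean is small and small when the mean is large, whether or not there is excess variation. The article nevertheless presents a large ratio as the definition of overdispersion.

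The rule chooses the error model for two prespecified tests on the primary outcome measure: change over time, and whether the arms diverge over time. A criterion that responds to the size of the mean can fail in two ways. It can fire on data that are exactly Poisson, in which case it checks nothing. Or it can stay silent on data with real excess variance, in which case Poisson standard errors are too small and the Wald tests reject too often.

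**Working it through.** The article states no figure for this rule, so there is none to reproduce. The check applies the rule to the article's own rates.

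**Inputs from the article**
- Planned rate: 0.36 per person-year, so 0.36/12 = 0.03 per person-month.
- Rate in the previous study: 0.78 per person-year, so 0.78/12 = 0.065 per person-month.
- Follow-up: "We also assume a median monitoring time of 18 months", so 0.36 × 1.5 = 0.54 expected acts per participant.
- Group size: "we will need 368 participants to have 90% power" before inflation, 368/2 = 184 per side of a factorial comparison; after inflation "the total required sample size is 442", 442/2 = 221 per side.

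**Assumption.** Overdispersion is modelled as negative binomial, with variance m + k·m² for a participant's count with mean m. The article gives no dispersion, so k from 0.5 to 10 is an assumed range.

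**Step 1: what the rule sees.** For Poisson data SD/mean = 1/√m and variance/mean = 1. For participant-months, √0.03 = 0.173 and 0.173/0.03 = 5.77. For pooled totals with all 221 followed, m = 221 × 0.03 = 6.63, √6.63 = 2.57 and 2.57/6.63 = 0.39.

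| Counting unit | Mean | SD/mean, pure Poisson | SD/mean, k = 10 | Variance/mean, k = 10 |
|---|---|---|---|---|
| Participant-month | 0.03 | 5.77 | 6.58 | 1.30 |
| Monthly total, 184 people | 5.52 | 0.43 | 0.49 | 1.30 |
| Monthly total, 221 people | 6.63 | 0.39 | 0.44 | 1.30 |
| Participant over 18 months | 0.54 | 1.36 | 3.44 | 6.4 |

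At the previous study's rate, pure Poisson participant-months still give 1/√0.065 = 3.92. One simulated set of 442 × 18 purely Poisson participant-months gave SD/mean 5.81 and variance/mean 0.996. The rule would have fired; a variance-to-mean comparison would not.

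**Step 2: when the rule can fire on pooled totals.** SD equals the mean when the variance equals the squared mean, that is, when variance/mean equals the mean. That requires a variance 6.63 times the mean for 221 people, or 5.52 times for 184. At 4 times Poisson variance and 221 people, SD = √(4 × 6.63) = 5.15 and 5.15/6.63 = 0.78, so the rule stays silent.

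**Step 3: cost if Poisson is wrongly kept.** If the true variance is V times Poisson, a nominal two-sided 5% Wald test has size 2 × (1 − Φ(1.96/√V)):
- V = 1.3: 8.6%
- V = 2: 16.6%
- V = 4: 32.7%

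**Step 4: how plausible these values of V are.** For pooled totals of participants who vary independently each month, V = 1 + k·m with m = 0.03. Then V = 1.3 needs k = 10, V = 2 needs k of about 33, and V = 4 needs k = 100. A simulation of pooled totals (221 per side, 18 months, 20% random dropout, Poisson Wald tests of linear trend and of time by group, 1,500 runs per setting) gave these sizes:
- Stable differences between participants, k = 10: about 5 to 6%. The same people contribute each month, so their differences largely cancel out of a time trend.
- Variation independent each month, k = 10: about 8 to 11%.
- Six-month bursts of behaviour, k = 10: about 20 to 24%. Most of this comes from correlation between months.

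In none of these runs did the SD of a group's monthly totals exceed their mean.

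**The case against.** The article names the concept it wants, so this may be a slip of one word for variance. That is plausible, but the sentence as printed defines a different condition and would be applied as written.

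The stronger objection concerns consequences. The outcome is built from daily data on each participant, so participant-month records are a natural reading. The rule then leads to negative binomial, which contains Poisson as a limit, and little is lost. This stands. The same section also sums acts by group, however, so pooled totals cannot be ruled out.

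Three stronger readings are tempting, and the documents do not support them.
- A reader might infer that the tests will run at 33%. That figure needs four times Poisson variance. The article gives no dispersion, and Step 4 shows that this needs a very large k at the planned rate.
- A reader might infer that the rule ignores the data altogether. Per participant over 18 months, SD/mean does respond to dispersion (1.36 to 3.44). It is the fixed 1-month interval that makes the response negligible.
- A reader might infer that the noninferiority conclusion is at risk. It rests on crude incidence rate ratios, to which this rule is not applied. Nor does the rule enter the sample size; that section is used here only for its rates and group sizes.

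**Conclusion.** Wrong as written, minor severity. The stated criterion is not overdispersion. At 1-month intervals and the article's own rates, the counting unit largely settles the outcome: SD/mean is about 5.8 to 6.6 for participant-months and about 0.4 to 0.5 for pooled monthly totals, over dispersion from none to k = 10. With participant-months the check is redundant. With pooled totals real overdispersion would be missed, and the change-over-time and time-by-arm tests could be anti-conservative, with size of about 9%, 17% or 33% under assumed variance inflation of 1.3, 2 or 4. The error in the definition needs no assumption. The size of the harm rests on pooled counting and on a dispersion that the article does not give.

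**What to change.** State that the count is per participant-month, and replace the condition in parentheses with: *negative-binomial regression if the variance exceeds the mean, judged by Pearson chi-square/df or a test of the dispersion parameter*. Exact Poisson data give variance/mean of 1 at every counting unit, and the ratio rises with dispersion, so this criterion measures what the sentence intends. Using an overdispersion-robust model from the outset, without a pre-test, would also work, but that is a preference and not needed to correct the error. A variance-to-mean check does not measure correlation between months and should not be relied on for that.

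The cost is one line of wording, with no extra data or resources, and no change to the primary comparison or the sample size.

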#### Secondary Outcomes

We will assess intracellular concentrations of TFV-DP and FTC-TP using DBSs collected at month 12 in all participants using daily PrEP. The lower limit of detection is determined as 25 fmol/punch and 50 fmol/punch for TFV-DP and FTC-TP, respectively. The distribution of the intracellular concentrations of TFV-DP and FTC-TP will be compared between daily PrEP users in (1) online PrEP care versus in-clinic PrEP care and (2) monitoring every 6 months versus monitoring every 3 months, using a rank-sum test. In a secondary analysis, the log-transformed values will be compared using a linear regression.

The incidence rates of HIV infection and TFV/FTC-resistant HIV infection, and the incidence rates of bacterial STIs (ie, chlamydia, gonorrhea, and syphilis), HCV infection, and eGFR of less than 60 mL/min/1.73m^2^ will be assessed. The incidence rates are calculated by dividing the number of diagnoses by the person-years of observation. The incidence rates will be compared for (1) online PrEP care versus in-clinic PrEP care and (2) monitoring every 6 months versus monitoring every 3 months.

Retention in PrEP care is defined as having had a PrEP prescription no longer than 8 months ago. Participants will be considered lost to follow-up when they do not complete a PrEP monitoring visit at month 18 within 2 months of the planned date. They will be regarded as lost to follow-up from the date of the last contact with the study (ie, completed a diary, questionnaire, or consultation). We will compare proportions of participants who are retained in PrEP care or are lost to follow-up for (1) online PrEP care versus in-clinic PrEP care and (2) monitoring every 6 months versus monitoring every 3 months, using the Pearson χ^2^ test.

Satisfaction with PrEP care will be compared between study arms. Furthermore, we will analyze how usability of the online PrEP service differs between online-mediated PrEP care every 3 months and every 6 months. For these analyses, we will use the Wilcoxon signed-rank test of the Likert score outcomes.

We will investigate the associations between sociodemographic and psychosocial determinants and the incidence rates of unprotected acts; HIV infection, STIs, and HCV infection; retention in PrEP care; and loss to follow-up. A wide range of parameters, mentioned in the Data Collection Methods section, will be included in our analyses. The analyses will involve logistic models, Cox proportional hazards models, and Poisson regression models.

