Limiting the number of in-clinic visits through a reduction in the frequency of PrEP monitoring may pose challenges for the timely screening of HIV and other STIs. Regular HIV testing during PrEP use is essential to identify breakthrough HIV infections in suboptimally adherent PrEP users and, rarely, in highly adherent PrEP users [35,36]. It allows for commencing HIV treatment as soon as possible and avoiding onward transmission and the development or transmission of drug-resistant strains. While the current guidelines recommend HIV testing every 3 to 6 months [8-12], few studies have formally investigated the impact of HIV screening frequency on PrEP adherence [8]. A lower frequency of contact moments and HIV testing may negatively affect PrEP intake. One randomized noninferiority trial in Kenya found similar PrEP adherence in adults with dispensing of PrEP every 6 months at the clinic combined with home-sampled HIV testing at 3 months after dispensing and in adults with dispensing of PrEP and HIV testing every 3 months at the clinic as the standard of care [37]. More evidence from other regions and from different groups of PrEP users is needed to further evaluate the implications of reduced frequency of monitoring. Particularly in high income settings with low HIV prevalence and high community-level PrEP uptake and PrEP adherence, HIV testing every 6 months might be sufficient. PrEP monitoring visits for men who have sex with men (MSM) in these settings are commonly combined with STI testing, but the optimal frequency of STI screening among MSM who use PrEP is unknown [2,22,38]. On the one hand, reducing the frequency of PrEP monitoring might lead to delayed diagnosis and treatment of asymptomatic STIs and onward transmission. On the other hand, it might avoid antibiotic use related to asymptomatic chlamydia and gonorrhea [39-41], and a lower STI screening frequency might be sufficient for MSM with lower levels of sexual activity.

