### Study Setting

The EZI-PrEP study will be embedded in the government-funded National PrEP Pilot Program (NPP) that plans to run from August 2019 until July 2024 [47]. This program provides PrEP care to persons at high risk for HIV infection, notably MSM and TGDP, and is implemented by the sexual health centers (SHCs) of the public health service (PHS) regions throughout the Netherlands. The PrEP care offered consists of in-clinic monitoring visits every 3 months that are free of charge. PrEP tablets are provided at a reduced price of €7.50 (US $7.88) per 30 tablets (paid out-of-pocket by the PrEP user) and are provided only to those completing a monitoring visit. Following the Dutch PrEP guidelines applicable at the time when the study started (ie, April 15, 2019 [10]), each PrEP monitoring visit includes screening for HIV infection, bacterial STIs, and HCV infection, and, every 6 months, screening for kidney function (Table 1). It also includes counseling based on motivational interviewing techniques to stimulate informed and conscious decision-making by PrEP users in relation to their own sexual health, PrEP intake, and usage of other HIV-prevention strategies. PrEP naïve people are allowed to commence PrEP immediately after screening and counseling, and have to return to the SHC after the first month of PrEP use for repeat HIV testing. Three months after commencing PrEP, routine PrEP care begins with the first in-clinic monitoring visit (performed every 3 months). Individuals are allowed to test for HIV, STIs, and HCV free of charge in between regular PrEP monitoring visits at their own initiative. Individuals can freely choose and switch between daily or event-driven PrEP regimens. These guidelines have since been updated in 2022, with the most relevant modification being that the monitoring frequency may be adapted under certain individual cases [11].

**Table 1 table1:** Overview of testing for HIV infection, sexually transmitted infections, hepatitis C virus infection, and kidney function as part of routine pre-exposure prophylaxis care for each EZI-PrEP study visit at sexual health centers in the Netherlands (based on Dutch national pre-exposure prophylaxis guidelines; April 19, 2019).

Laboratory measurement	Inclusion	Months								
		1	3	6	9	12	15	18	21	24
HIV	✓	✓^a^	✓	✓	✓	✓	✓	✓	✓	✓
Syphilis	✓		✓	✓	✓	✓	✓	✓	✓	✓
*Chlamydia trachomatis*	✓		✓	✓	✓	✓	✓	✓	✓	✓
*Neisseria gonorrhoeae*	✓		✓	✓	✓	✓	✓	✓	✓	✓
HCV^b^	✓		✓	✓	✓	✓	✓	✓	✓	✓

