### Interventions

#### PrEP Care Every 6 Months

Participants in arms 2 and 4 (Figure 1) will receive PrEP care every 6 months. All study participants, irrespective of study arm, will be allowed to get screened free of charge for HIV and STIs in between scheduled PrEP monitoring visits (eg, after a partner notification for an STI or in case of STI-related symptoms). To allow for monitoring in between testing, we will ask participants to visit the SHC where they receive PrEP care.

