The EZI-PrEP study will contribute crucial data to the ongoing debate on optimal HIV and STI screening frequency for MSM who use PrEP. By comparing incidence rates of HIV infection, STIs, and HCV infection between the 3-month and 6-month monitoring study arms, we will provide evidence on the impact of testing every 6 months on STI diagnosis and treatment. If noninferiority in terms of PrEP adherence is concluded and STI incidence rates are similar between the 6-month and 3-month monitoring arms, a stronger case can be made to offer PrEP monitoring every 6 months as the standard of care. If STI incidence rates are not similar between the study arms, we will be able to examine to what extent this is related to particular sociodemographic, sexual behavior, or psychosocial factors and advise on implementation accordingly. EZI-PrEP study participants will be allowed to test for HIV, STIs, and HCV in between regular PrEP monitoring visits at their own initiative. The EZI-PrEP study will also be able to quantify the extent to which in-between visits occur among PrEP users receiving monitoring every 6 months.

Since adherence to the PrEP intake regimen is crucial for its effectiveness [3,5-7], having a thorough understanding of enabling and disenabling factors of PrEP adherence is important. The EZI-PrEP study will provide new insights on the associations between sociodemographic and psychosocial variables on the one hand and PrEP adherence on the other hand. Insights into the role of such sociodemographic and psychological factors in the context of adherence may be used to further improve the content or conduct of PrEP consultations and inform interventions that support PrEP adherence. Furthermore, we will investigate the relationship of these factors with PrEP adherence, STIs, retention, and satisfaction with PrEP care, according to the study arm. The results of these analyses could be used to determine if these new PrEP care modalities should be implemented widely or should be offered to specific subpopulations.

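### The 6- v 3-month STI comparison counts diagnoses per person-year under 4 v 8 routine screens, so similar rates alone cannot support 6-month monitoring

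*Protocol article*

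**What the plan says.** Secondary Outcomes fixes the estimator for HIV, bacterial STIs and HCV: "The incidence rates are calculated by dividing the number of diagnoses by the person-years of observation". It then fixes two direct contrasts of these rates, one by mode of care and one by frequency of monitoring. The denominator is time. The article states no adjustment for tests done, no restriction to shared test times, and no caution about detection.

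Study Setting ties testing to visits: "each PrEP monitoring visit includes screening for HIV infection, bacterial STIs, and HCV infection". The section on the reduced schedule says: "Participants in arms 2 and 4 (Figure 1) will receive PrEP care every 6 months". Study Design gives the follow-up: "For each individual participant, the planned observation time is 24 months, starting after eligibility screening and enrollment". Testing between visits is optional: "All study participants, irrespective of study arm, will be allowed to get screened free of charge for HIV and STIs in between scheduled PrEP monitoring".

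The Introduction recognises that "reducing the frequency of PrEP monitoring might lead to delayed diagnosis and treatment of asymptomatic STIs and onward transmission". The Discussion nevertheless says that if adherence is noninferior and "STI incidence rates are similar between the 6-month and 3-month monitoring arms, a stronger case can be made" for 6-monthly monitoring as standard of care.

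**The concern.** The randomized factor is itself the frequency of looking for infection. An asymptomatic infection that clears before the next screen is never counted. Two acquisitions between screens can merge into one diagnosis. Both losses are larger when the interval is 6 months rather than 3. With identical acquisition, the 6-month arms are therefore expected to show fewer diagnoses per person-year.

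The consequence lies in the reading of a null result. If fewer diagnoses are expected under equal acquisition, then equal diagnosis rates are not evidence of equal infection. The Discussion sentence treats them as support for the less frequent schedule, and the measure cannot show the undiagnosed infection that the Introduction mentions.

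**Working it through.** The article gives no figure for this comparison, so there is none to reproduce.

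**1. Routine screens, from the documents.** Table 1 schedules syphilis, chlamydia and gonorrhea tests at inclusion and at months 3, 6, 9, 12, 15, 18, 21 and 24. The month 1 visit is for HIV only. The 3-month arms thus have 24/3 = 8 routine post-inclusion STI screens, and the 6-month arms have 24/6 = 4 (months 6, 12, 18, 24).

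**2. A check that needs no disease model.** If all diagnoses came from routine screens and the two groups had the same number per person-year, that number would come from half as many screens in the 6-month arms. Positivity per routine screen would then be 8/4 = 2 times as high there.

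**3. Simple model (durations assumed).** Infections are acquired evenly over time, are asymptomatic, and have an exponential untreated duration with mean D months. Screening with treatment takes place every T months.
- Share of infections detected: (D/T)(1 − exp(−T/D)).
- Positivity ratio at a visit, 6- v 3-month: (1 − exp(−6/D)) / (1 − exp(−3/D)).

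| D (months) | Detected, T = 3 | Detected, T = 6 | Diagnosis ratio | Positivity ratio |
|---|---|---|---|---|
| 3 | 0.632 | 0.432 | 0.68 | 1.37 |
| 6 | 0.787 | 0.632 | 0.80 | 1.61 |
| 12 | 0.885 | 0.787 | 0.89 | 1.78 |

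With equal acquisition the diagnosis ratio lies below 1 and the positivity ratio above 1. Neither isolates acquisition.

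**4. Model that allows reinfection.** Acquisition rate L per person-year, clearance rate c = 12/D per year, test and treat every T years:

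diagnoses per year = [L/(L + c)] × (1 − exp(−(L + c)T)) / T.

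Example with L = 0.6 and D = 6 months, so c = 2. At T = 0.5 the rate is 0.2308 × 0.7275/0.5 = 0.336. At T = 0.25 it is 0.2308 × 0.4780/0.25 = 0.441. The ratio is 0.76.

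Over L from 0.3 to 1.0 (all assumed), with equal L in both groups:

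| Mean duration | Ratio, all asymptomatic | Ratio, 30% symptomatic | True rate multiple in 6-month arms for an observed ratio of 1 |
|---|---|---|---|
| 3 months | 0.64–0.67 | 0.80–0.81 | 1.53–1.74 |
| 6 months | 0.74–0.78 | 0.85–0.86 | 1.30–1.49 |
| 12 months | 0.80–0.86 | 0.89–0.91 | 1.17–1.33 |
| 24 months | 0.84–0.91 | 0.91–0.95 | 1.11–1.25 |
| No clearance | 0.89–0.96 | 0.95–0.98 | 1.04–1.17 |

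The 30% column assumes that symptomatic infections are diagnosed at once in both groups; it treats them approximately, as a separate stream. The last column is for the all-asymptomatic case. Every scenario gives a ratio below 1.

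**5. Reach.** The online and in-clinic groups each pool one 3-month and one 6-month arm, so their planned screening is the same. Creatinine is scheduled every 6 months in Table 1, so the eGFR outcome is not affected. The primary outcome comes from the diary.

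**The case against.** A diagnosis rate is a legitimate outcome. The Discussion frames the comparison partly as the impact of 6-monthly testing on STI diagnosis and treatment, and diagnoses per person-year under each randomized schedule answer that question. This stands. The fault is confined to the label incidence and to reading similarity as reassurance.

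Testing intensity is not ignored. Testing behavior is a stated secondary aim, and the total number of STI consultations is to be compared. Reasons for consultation and testing outside the centers are collected, and in-between visits in the 6-month arms will be quantified. Free in-between testing and symptomatic presentation shrink the bias. This stands too, but such testing is optional, and the article does not link it to the STI rate. It would remove the bias only if it made up the whole difference in screening. How testing enters the models might be left to an analysis plan, but the estimator and its reading are stated here.

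Four stronger readings are tempting and not supported:
- A reader might infer that lower STI rates would also count in favor of 6-month monitoring. The Discussion says only similar. Dissimilar rates are to be examined against sociodemographic, behavioral and psychosocial factors.
- A reader might take the Discussion sentence as a decision rule. It also requires noninferior adherence, and it carries no STI margin or test.
- A reader might infer that the Introduction declares a harm that has to be assessed. It says delay might occur, and it names less antibiotic use for asymptomatic infection as a possible benefit.
- A reader might conclude that the ratio shows testing intensity alone, or that shared-visit positivity should replace it. The ratio also carries acquisition, and positivity depends on the schedule as well (1.37 to 1.78 under equal acquisition in step 3).

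**Conclusion.** The point holds for the frequency comparison of bacterial STIs, a secondary outcome. As defined, the ratio mixes acquisition with testing intensity and is biased downward for the 6-month arms. The direction follows from 4 v 8 routine screens, provided that voluntary testing does not close the gap.

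The size is not known from the documents. With equal acquisition it runs from about 0.64 (short-lived, all asymptomatic) to 0.98 (no clearance, 30% symptomatic). This rests on assumed durations of 3 months to no clearance, acquisition rates of 0.3 to 1.0 per person-year, and no other in-between testing. For persistent infections the effect is small. In the all-asymptomatic case, an observed ratio of 1 would correspond to true acquisition 1.04 to 1.74 times as high under 6-month monitoring. Similar diagnosis rates can therefore coexist with higher acquisition or more undiagnosed infection.

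**What to change.** 1. In Secondary Outcomes, call the STI measure a diagnosis rate. Report it by arm with tests per person-year, and show symptomatic and partner-notified diagnoses separately.
2. For the frequency comparison, add chlamydia, gonorrhea and syphilis positivity at the visits that all arms share (months 6, 12, 18 and 24), with clustering on participant (for example GEE logistic or log-binomial models). State that it measures infection burden under each schedule, not acquisition, and that treatment following the extra screens at months 3, 9, 15 and 21 is part of the schedule effect.
3. Reword the Discussion so that the STI argument for 6-month monitoring rests on both measures read together, not on similar diagnosis rates alone.

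The cost is a little more analysis and some rewording. Tests, diagnoses and reasons for consultation are already collected (Clinical Data). Shared-visit positivity uses fewer positives than all diagnoses, so it is less precise.
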